## Abstract

**Background:**

The COmmunity HEalth System InnovatiON (COHESION) project (2016–2019) was a 4-year collaboration between research teams from Mozambique, Nepal, Peru and Switzerland. It conducted formative health system research using tracer chronic conditions, non-communicable diseases (diabetes and hypertension) and one neglected tropical disease per country (schistosomiasis in Mozambique, leprosy in Nepal and neurocysticercosis in Peru).

Findings guided the co-creation of interventions to improve diagnosis and management through a participatory approach with communities, primary healthcare workers and regional health authorities.

As a continuation of this effort, the research team initiated the COHESION Implementation project (COHESION-I) with two objectives: (1) implement and evaluate the context-specific co-created interventions in Mozambique, Nepal and Peru (Component 1) and (2) adapt the COHESION approach to India, a country that did not benefit from a formative phase previously (Component 2). This protocol manuscript focuses on Component 1.

**Methods and analysis:**

A mixed-methods, pre–post quasi-experimental design will be used, including quantitative, qualitative, economic and process evaluations. Each country will have three arms: (1) co-created and co-designed interventions; (2) only co-designed intervention and (3) the usual care arm. Data will be collected longitudinally over 18 months to assess the effect of the interventions. The main outcomes include patient satisfaction (Patient Satisfaction Questionnaire Short Form), health system responsiveness (WHO responsiveness domains) and quality of life (EuroQol 5 dimensions 5 levels). The qualitative evaluation will explore how satisfaction is perceived among service users with chronic conditions and healthcare workers. Other outcomes per type of evaluation will be considered such as perceived value of health services, cost estimation and acceptability of the intervention components, among others.

**Ethics and dissemination:**

Approvals were obtained from Ethics Committees of Universidad Peruana Cayetano Heredia (Peru), Universidade Eduardo Mondale (Mozambique) and Nepal Health Research Council (Nepal). Results will be disseminated through peer-reviewed publications and scientific conferences.

**Trial registration number:**

NCT06989502.

STRENGTHS AND LIMITATIONS OF THIS STUDYThis protocol provides an approach for designing complex context-adapted interventions that engage the voices of diverse stakeholders in three low- and middle-income countries.Our research proposes a comprehensive evaluation framework integrating quantitative, qualitative, economic and process evaluation to assess intervention outcomes.The initial survey will inform about the individuals with the conditions studied, and the population satisfaction and responsiveness to adjust sample sizes per arm.The evaluation will focus on low-resources primary healthcare centres, where system constraints may limit effectiveness or it may have substantial impact due to these populations rarely receiving health interventions.

## Background

 The management of chronic diseases poses a problem to many health systems in low- and middle-income countries (LMIC) as health systems in these countries are not organised to provide long-term care.^1^,^3^ Managing chronic diseases requires a comprehensive health system, with regular availability of medicines, laboratory facilities, data collection tools, trained healthcare staff and educated and empowered service users.^1 4^

To address this, the Chronic Care Model was adapted to LMICs under the name of the Innovative Care for Chronic Conditions Framework (ICCCF).^4 5^ The ICCCF calls for a ‘paradigm shift’ to ensure that health systems are capable of organising care for chronic conditions and includes changes at policy level, health system and in communities. Sadly, in LMICs, the lowest utilisation of public health services is by the poor, those who need it the most, as these services are often not available or sensitive to their needs.^6 7^ Weaknesses in health systems and their inability to address the health needs of vulnerable populations, particularly at the primary healthcare (PHC) level, are well known barriers to achieving people-centred care.^8^ In order to reach this goal, it is essential to improve healthcare quality and strengthen the health system to ensure it is more responsive to people’s needs. Also, it has been shown that focusing on the community as recipients of care and the issues that affect healthcare workers, as providers of this care, can have better yields.^2^

The management of chronic diseases improves if the patient is satisfied with the health services.^9^ However, the evaluation of satisfaction is not always aligned with the performance of the health system and the use of responsiveness was proposed. Some challenges to measure satisfaction are that people living in vulnerable conditions may not always feel comfortable expressing their opinions through surveys, while interviews appear as a suitable strategy for people to share their views.^10^ These qualitative approaches allow us to elucidate service users’ expectations from the local health services, which are also crucial to understand whether a health system is considered responsive.^11^ In order to understand the underlying issues related to the provision of quality services, WHO proposed the health systems responsiveness framework, which is useful to focus on the interaction between service users and healthcare workers, going beyond specific diseases and leading to a true strengthening of the health system. For these reasons, patient satisfaction and responsiveness are good proxies of health system performance and useful to disentangle the complexity of the health system and evaluate its performance from a people-centred care perspective.

A recent cross-sectional study in middle-income countries on healthcare quality and health system responsiveness concluded that rigorous evaluations of interventions to improve quality of care and responsiveness are urgently needed, given the importance of both elements for achieving effective universal health coverage (UHC).^3^ Furthermore, the WHO states that there is a positive association between health outcomes and responsiveness,^11^ and evidence suggests that demand-side barriers may be as important as supply factors in deterring service users from obtaining chronic care.^12^ Although many state that co-designed interventions are more successful in achieving satisfaction and better health outcomes, this has not been truly tested.^13^ Therefore, new approaches are needed to generate evidence from health systems research in LMIC about the practices to improve patient satisfaction and responsiveness derived from the expectations and demands of those who provide care (healthcare workers) and those who use the health system (service users).

### Objectives

To implement and evaluate, at the PHC level, the co-created/co-designed interventions in the three countries (Mozambique, Nepal and Peru), focusing on non-communicable diseases (NCDs) (ie, diabetes, hypertension) and neglected tropical diseases (NTDs) (ie, schistosomiasis in Mozambique, leprosy in Nepal and neurocysticercosis (NCC) in Peru) to improve patient satisfaction and health system responsiveness. The present protocol has a comprehensive approach to evaluate their results and, therefore, the general objective is subdivided into four subcomponents of evaluation:

*Quantitative evaluation*: To evaluate changes in the level of patient satisfaction and health system responsiveness among PHC users living with a chronic condition. For this, a pre–post strategy approach will be used with two assessments before the implementation of the intervention, one assessment during the intervention and two assessments after the intervention, with a 3-month time gap between assessments.*Qualitative evaluation*: To explore the differences that exist between the perceptions of PHC users living with a chronic condition about the local public health services (*through time*)*,* and the perceived roles and responsibilities healthcare workers feel they have toward PHC users (*over time*)*,* and how these differences change (increase or decrease) as the interventions are implemented.*Economic evaluation*: To assess the costs and cost-effectiveness of co-designed interventions compared with usual care to improve the health system responsiveness and satisfaction of people with chronic conditions at the PHC level.*Process evaluation*: To explore contextual factors that may impact the implementation of COmmunity HEalth System InnovatiON Implementation (COHESION-I), describe the implementation process of the project and identify the mechanisms through which the implemented intervention has an impact (or not) in the arms that receive the intervention.

### Hypotheses

The primary hypothesis of the COHESION-I study is that patient satisfaction and health system responsiveness will be higher in the intervention arms (co-creation/co-design and only co-design interventions) compared with the usual care arm in each country. We also hypothesise that, between active interventions, greater satisfaction and responsiveness will be observed among those in the co-created/co-design intervention compared with only co-design intervention.

## Methods and analysis

### Context

The COHESION project was a 3-year project that started in 2016 as a collaboration between teams from Mozambique, Nepal, Peru and Switzerland funded by the Swiss National Science Foundation and the Swiss Agency for Development and Cooperation as part of the Research for Development programme (r4d Programme). The COHESION project conducted formative research at policy, health system and community levels using NCDs and NTDs as tracer conditions. The NCDs were diabetes and hypertension (HTP), and in the case of NTDs, it included schistosomiasis in Mozambique, leprosy in Nepal and epilepsy resulting from NCC in Peru.

The results from this formative research were used to identify adequate interventions through a participatory approach with communities, healthcare workers from PHC and regional health authorities (co-creation). Meetings with different stakeholders took place in 2017 and 2018 to propose context-relevant interventions oriented to address the challenges of providing care for people affected by diabetes, HTP and the selected NTDs (schistosomiasis, leprosy and epilepsy due to sequelae of NCC). During the meetings, participants provided feedback regarding problems and potential solutions for chronic care and health services in general and proposed possible areas of intervention.^14^ According to the needs in each country, other activities were used to strengthen the health system response and achieve a more effective communication. The results of the co-creation are available in online supplemental table 1.

### COHESION-I

The COHESION-I project is the continuation of the COHESION project. It will be implemented between 2022 and 2026 (4 years) and has two components. Component 1 involves Peru, Mozambique and Nepal and has two parts: the first one is the co-design process, and the second one is the implementation and evaluation of the interventions. Component 2 is the optimisation of the process of formative research, co-creation and co-design in a new country, India. This protocol describes the work to implement Component 1.

The project defines co-design as the process of involving different stakeholders in designing or refining interventions for a prespecified problem, using participatory approaches to generate creative strategies.^15^ Co-design in COHESION-I seeks to refine the interventions previously co-created (online supplemental table 1). The research team is currently co-designing communication materials, training formats for healthcare workers and coordinating health facility improvements. This process ensures the proposed interventions reflect people’s values, perceptions and expectations around health service delivery.^16^ The three countries initiated the fieldwork activities of the co-design process in May 2023, and it will end in early 2026. This manuscript protocol focuses on the implementation and evaluation of the co-designed interventions.

### Setting

The implementation of interventions in COHESION-I will be conducted in Mozambique, Nepal and Peru, countries with different characteristics and health systems responses to chronic conditions as it has been described in detail elsewhere.^17^ The sites were selected during the first phase of the project to capture diversity in geography, socioeconomic conditions and health systems structures in three different continents. Moreover, selected sites prioritised locations where the co-creation approach had been applied, and they included urban and rural sites.^14^ Each country will have two intervention arms and one control arm.

### Health system in the selected countries

This section provides a brief description of the health systems in each of the countries to understand better the contexts where the COHESION-I interventions will be implemented and evaluated.

#### Nepal

Every citizen in Nepal is entitled to free basic health services as health is considered a fundamental human right in the constitution. The health system in Nepal is decentralised and structured in three tiers: local/municipal level, provincial level and federal level. Provision of primary health services is the responsibility of local government. Provincial government is responsible for delivery of basic health services through provincial hospitals and coordinating with local and federal levels. The federal government is responsible for policy formulation, budget allocation and delivery of specialised healthcare through national hospitals. Primary health services at local level are delivered through PHC centres, Health posts, Basic Healthcare Service Centres, Urban Health Centres and primary level hospitals.^18^ Besides this, the primary level often extends its services to communities through PHC outreach clinics, female community health volunteers and immunisation clinics.^18^ In order to ensure UHC, the Government of Nepal has employed Social Health Insurance Schemes that offer financial protection to service recipients in PHC centres and every tier of hospitals.^19^

#### Mozambique

The Mozambican health system created after the independence of the country in 1975 is based on the Alma Ata conference, giving the higher priority to the PHC system.^20^ The health sytem in Mozambique is structured in primary, secondary and tertiary care. The PHC centres are public; although the network has some geographic gaps, the system was designed predominantly to take care of infectious diseases that were predominant.^21^ This means that NCDs are still a challenge in terms of training of the health team, availability of diagnostic basic instruments and availability of drugs. The major priorities for the system are HIV, tuberculosis and malaria programmes that are almost totally financed by the external help. All the PHC activity is almost free for all. The private health system is limited to the big cities and is very small and non-significant. Most of the population is not covered by a system of health insurance.^21 22^

#### Peru

The Peruvian health system is a fragmented, labour-based health system, with stewardship responsibilities falling under the Ministry of Health. The Ministry of Health provides care for people with low income (70% of the population), while Social Security offers services to formal workers and their families (20% of the population). There are also health services for the armed forces and also a private sector.^23^ The health system is organised in primary, secondary and tertiary healthcare levels and specialised institutes. Each of the 28 health regions in the country is responsible for the resource allocation to the three levels.^24^

### Study design

The COHESION-I project will implement a co-created/co-designed intervention and concurrently evaluate the intervention using a mixed-methods approach that includes a pre–post quasi-experimental study to assess the effect of the co-designed and co-created interventions, the co-design intervention on the primary and secondary outcomes, compared with the usual care. The project will have four types of evaluations that have a different approach and design. These are the following:

#### Quantitative evaluation

The quantitative evaluation will set two different approaches. First, an initial survey will be conducted to have appropriate estimates of the PHC users and validate tools to be used in the intervention assessment. Second, a quasi-experimental approach will be used to assess the effect of the co-designed and co-created interventions on the primary and secondary outcomes compared with the usual care in an 18-month period.

#### Qualitative evaluation

The qualitative evaluation will include two studies: a qualitative longitudinal study with local PHC users and a qualitative study with healthcare workers. The qualitative evaluation will be guided by the ‘lay evaluation of healthcare’ theoretical framework proposed by Calnan,^25^ value theory^26^,^29^ and the WHO responsiveness framework.^30^

The longitudinal qualitative study aims to explore the experiences of adult women and men living with diabetes, hypertension or the specific neglected tropical disease and how they unfold *through time*^31^. The data will be collected at different moments (initial survey, moments 3 and 5) with the same participants through in-depth and semi-structured interviews. Photo-elicitation will be used, if participants accept, to evoke conversations during the interviews.

The qualitative study with healthcare workers will examine *over time* the perceived roles and responsibilities of healthcare workers in providing care for PHC users with chronic conditions. The interviews will be conducted at three different moments, before, during and after the intervention implementation.

#### Economic evaluation

An economic evaluation will be conducted, comparing two arms: care-as-usual (control) and the implementation of the co-design interventions. The evaluation will be conducted in three distinct phases: (1) implementation only, (2) co-design and implementation, and (3) co-creation, co-design and implementation. A cost-effectiveness and cost–utility analysis will be conducted. The study will adopt a dual perspective, examining both the healthcare sector (ie, the Ministry of Health of each country) and the societal (ie, households) perspectives. The time horizon over which costs and consequences will be evaluated is 3 years, and the discount rate will be 10% according to national rates. The relatively short time horizon and the discount rate will be considered as parameters in a sensitivity analysis.

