#### Economic analysis

A detailed micro-costing of the resources will be implemented, and descriptive statistics of the implementation resources and costs of the different strategies and usual care will be presented. Implementation and healthcare costs will be included in the cost-effectiveness analysis from the healthcare perspective. In addition to these costs, other direct and indirect costs will be included in the analysis from a societal perspective. The primary outcome of the economic evaluation will be the incremental cost-effectiveness ratio.

A sensitivity analysis will be performed by varying parameters such as the discount rate, among others, to account for uncertainty.

For cost-effectiveness analysis, primary outcomes indicators will be used (table 3). Assessment will consider patient satisfaction (PSQ-18) and health system responsiveness as primary outcomes. Each country team will set cut-off points to identify community satisfaction with services. Incremental cost-effectiveness ratios will be calculated as the difference in costs and effectiveness between intervention and usual care arms using both alternatives. For cost–utility analysis, we will evaluate two alternatives using EQ-5D-5L as outcome for quality-of-life measurement. Utility values will be derived by combining EQ-5D-5L results with pre-existing set of values (‘tariffs’). EQ-5D-5L and corresponding country value sets are validated in Nepal and Peru; Mozambique will use the international standard value set. Quality-adjusted life-years (QALYs) will be calculated by multiplying utility value for each alternative during 10-year incremental cost–utility ratios, which will be calculated using costs and QALY differential.

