The co-creation approach ensures the involvement of diverse stakeholders to develop an intervention and/or implement it.^15 55^ In this project, we are using co-creation and co-design; the first one refers to the development and design of an intervention with the participation of stakeholders, whereas co-design is the refinement of the components of the intervention to develop the outputs and have them ready for being delivered.^15 56^ Nevertheless, there is a lack of studies that scientifically evaluated the impact of co-created/co-designed interventions, and for that reason, the current study is relevant. It is comparing two arms against the usual care: one arm where the sites participate in co-creation and co-design and a second arm where only co-design was applied. The assumption is that co-creation is necessary to design tailored interventions, but once co-created, this intervention can be implemented in sites with similar characteristics using only co-designed.^57 58^

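### The economic evaluation is framed as two arms in a three-arm study, so the separately costed co-creation layer has no incremental effect to go with it

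*Protocol article*

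**What the plan says.** All references are to the protocol article.

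- **Arms.** Setting: "Each country will have two intervention arms and one control arm". The Discussion describes the active arms as "one arm where the sites participate in co-creation and co-design and a second arm where only co-design was applied".
- **Hypothesis between active arms.** Hypotheses: "greater satisfaction and responsiveness will be observed among those in the co-created/co-design intervention compared with only co-design intervention".
- **Economic objective.** Objectives: "To assess the costs and cost-effectiveness of co-designed interventions compared with usual care". Usual care is the only comparator named.
- **Economic design.** Study design, Economic evaluation: "An economic evaluation will be conducted, comparing two arms: care-as-usual (control) and the implementation of the co-design interventions". The same paragraph then sets three phases: "1) implementation only, (2) co-design and implementation, and (3) co-creation, co-design and implementation".
- **Ratios.** Economic analysis: "Incremental cost-effectiveness ratios will be calculated as the difference in costs and effectiveness between intervention and usual care arms using both alternatives".
- **Costing.** The Economic evaluation section on data collection describes one intervention arm in the singular. Its information comes from the teams that ran both co-creation and co-design.
- **Purpose.** The Discussion says the economic evaluation will give decision-makers information on what co-creation and co-design cost and yield.

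**The concern.** What sets this study apart is the contrast between sites that took part in co-creation and co-design and sites that took part in co-design only. For a health ministry the economic question is whether the extra participatory work is worth its cost. Answering it takes an incremental cost and an incremental effect for the same contrast. The plan provides for the first and does not define the second.

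The two-arm statement also leaves open how the co-created arm enters: pooled with the other active arm, left out, or analysed separately. These choices give different ratios. A reader of the results could not tell whether the ratio for the third phase rests on the effect in the co-created arm or on an effect shared with the co-designed-only arm.

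**Working it through.** **1. The plan's own figure.** The point disputes no stated figure. The sample size is shared by the quantitative and economic evaluations, so I reproduce it first.

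- Inputs (Sample size for the quantitative and economic evaluation): PSQ-18 means 3.38 to 3.44 in control and 3.37 to 3.69 in intervention; baseline SDs 0.48 and 0.52 (mean 0.50); correlation 0.3; type I error 0.05 (two-sided assumed); power 90%; loss 10%.
- Difference in changes: (3.69 − 3.37) − (3.44 − 3.38) = 0.26.
- Variance of a change: 2 × 0.50² × (1 − 0.3) = 0.35.
- n per arm: 2 × 0.35 × (1.960 + 1.282)² / 0.26² = 108.8, so 109. Then 109 / 0.9 = 121.1, against 121 in the article.

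**2. Matching cost phases to arms.** The natural reading sets each phase beside the arm with the same make-up. The article does not state this mapping.

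| Cost phase | Arm with that make-up |
|---|---|
| Implementation only | None: both active arms include co-design |
| Co-design and implementation | Co-designed-only arm, although its intervention was already co-created |
| Co-creation, co-design and implementation | Co-created/co-designed arm |

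Subtracting the second phase from the third isolates the cost of co-creation. The effect that belongs with it is the co-created/co-designed arm minus the co-designed-only arm. No ratio in Economic analysis uses that difference.

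**3. What a two-arm effect leaves undetermined.** Assume, for illustration only, that the active arms are pooled in equal numbers. Let E1 be the effect versus usual care in the co-created/co-designed arm and E2 that in the co-designed-only arm. The pooled effect is (E1 + E2)/2. Let *c* > 0 be the extra cost per participant of the co-creation layer.

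| E1 | E2 | Pooled | E1 − E2 | Active-versus-active ratio |
|---|---|---|---|---|
| 0.26 | 0.26 | 0.26 | 0 | extra cost, no gain |
| 0.36 | 0.16 | 0.26 | 0.20 | *c*/0.20 = 5.0*c* |
| 0.46 | 0.06 | 0.26 | 0.40 | *c*/0.40 = 2.5*c* |

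All three rows give the same two-arm result. If one effect of 0.26 served both phases, moving from the second to the third would raise the ratio against usual care by *c*/0.26 = 3.85*c* in every row. Co-creation could then only look worse.

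**4. Precision of the missing contrast.** With 109 evaluable per arm, the standard error of a difference in changes is √(2 × 0.35/109) = 0.080, so the 95% half-width is 1.96 × 0.080 = 0.16 points. The article also prints 242 per arm. On that figure 242 × 0.9 ≈ 218 are evaluable and the half-width is 1.96 × √(0.70/218) = 0.11. Clustering by health centre is ignored and would widen both. For an observed increment of 0.20 and 109 per arm, the interval is about 0.04 to 0.36. With cost held fixed, the ratio runs from about 2.8*c* to 23*c*.

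**The case against.** The strongest defence is that the economic part agrees with its own objective, which names usual care as comparator. The hypothesis between active arms concerns satisfaction and responsiveness, not cost-effectiveness. The Discussion sentence does not literally promise a cost per outcome for adding co-creation. The last two phases mirror the two active arms, and the reference to both alternatives in Economic analysis could mean two strategies as easily as two outcomes. This stands in part: pooling is not stated, and the cost of co-creation can be isolated. It does not remove the conflict, because the text says two arms where the study has three and pairs no effect with the separated cost.

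Two further objections shape the remedy and stand. First, the co-designed-only arm delivers an intervention that came out of the earlier co-creation (COHESION-I, Intervention, Discussion). Charging it only for co-design and implementation omits a cost on which its effect depends. Second, implementation only is a reasonable adoption scenario for a ministry that treats development as already paid for, provided its assumed effect is labelled.

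Stronger readings are tempting but unsupported:

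- *That the ratios use raw follow-up differences and so absorb baseline imbalance.* Economic analysis speaks of a difference and is silent on the estimator. Primary endpoint analysis plans longitudinal models with confounders for the same outcomes, and baselines are collected. Nor does the sample size section give unequal starting levels as its reason for using the interaction.
- *That cut-offs must be common to all countries.* The article says "Each country team will set cut-off points to identify community satisfaction with services". With hypotheses stated per country and tools to be validated and adapted from the initial survey, that is a defensible choice.

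**Conclusion.** The point holds. The economic comparison is written for two arms in a study with two distinct active arms and usual care. As it stands, the plan cannot give the incremental cost-effectiveness of adding co-creation. It can give the cost of co-creation but defines no matching effect, and its implementation-only phase has no observed arm behind it.

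The size cannot be fixed from the article, which gives no costs and no separate effects for the active arms. Under equal pooling, one two-arm effect of 0.26 covers co-creation increments at least from 0 to 0.40 points. That range depends on the pooling assumption, on the three illustrative splits and on the planning data, and is not a forecast. If the active arms are in fact to be analysed separately, the defect is one of unclear wording plus the missing active-versus-active ratio. The primary satisfaction and responsiveness analyses are not affected.

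**What to change.** Amend the Economic evaluation section under Study design and the Economic analysis section as follows.

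1. Define the comparison over all three arms within each country: each active arm versus usual care, and co-created/co-designed versus co-designed only. Each contrast uses its own observed effect.
2. State which cost layers enter each contrast. Report the co-designed-only ratio both with and without the original co-creation cost.
3. Interpret the active-versus-active contrast as the value of local participation in co-creation, not of co-creation as such.
4. Label implementation only as a scenario that assumes the effect seen in the co-designed arms.
5. State that incremental effects come from the longitudinal, confounder-adjusted models in Primary endpoint analysis.

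**Cost.** Effect data are already planned in all arms, so no new outcome collection is needed. Implementation costs must be tallied separately for each active arm. Logbooks are kept in each health centre, which should make this feasible, but the article describes costing for one intervention arm and does not confirm it. The active-versus-active ratio will be imprecise and should be shown with its uncertainty. In December 2025 Peru was at Moment 3 and the other two countries at Moment 2, so the rules could still be fixed before the Moment 5 data that the economic outcomes use.
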